## Methods and analysis

### Study design and setting

The LAP-PIE trial is a UK multicentre feasibility study that will recruit 50 patients with LAPC in whom the disease has remained localised and unresectable following FOLFIRINOX. Patients will receive 3–6 months of FOLFIRINOX prior to restaging and being assessed for study eligibility. All participants will be offered palliative chemotherapy according to standard centre protocols and half will also be offered one IRE procedure. If new agents for second-line therapy are approved by NICE prior to or during the LAP-PIE trial, these can be offered in the second-line chemotherapy arm and following IRE therapy if considered appropriate by the treating oncologist. Patients randomised to the control arm who have benefitted from initial chemotherapy with FOLFIRINOX may continue on the same regimen if this deemed appropriate by the treating oncologist. It is an open-label study. Patient enrolment is expected to last 15 months assuming a recruitment rate of 0.8 patients per site per month across seven UK centres and an opening site rate of 0.5 per month. The trial will be conducted in specialist pancreas cancer centres. IRE will be delivered across all trial centres. Interventional radiologists performing pancreas IRE in the trial will have performed a minimum of five previous pancreas or liver IRE ablations prior to administrating IRE to participants enrolled in the trial. Additional technical support will be available from manufacturers of the equipment, AngioDynamics. Figure 1 summarises the trial design and table 1 demonstrates the schedule of enrolment, interventions and assessments.

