**Methods and analysis:**

Eligible patients with LAPC who have undergone first-line 5-FluoroUracil, Leucovorin, Irinotecan and Oxaliplatin chemotherapy will be randomised to receive either a single session of IRE followed by (if indicated) further chemotherapy or to chemotherapy alone (standard of care). Fifty patients from up to seven specialist pancreas centres in the UK will be recruited over a period of 15 months. Trial follow-up will be 12 months. The primary outcome measure is ability to recruit. Secondary objectives include practicality and technical success of treatment, acceptability of treatment to patients and clinicians and safety of treatment. A qualitative study has been incorporated to evaluate the patient and clinician perspective of the locally advanced pancreatic cancer with percutaneous irreversible electroporation trial. It is likely that the data obtained will guide the structure, the primary outcome measure, the power and the duration of a subsequent multicentre randomised controlled trial aimed at establishing the clinical efficiency of pancreas IRE therapy. Indicative procedure-related costings will be collected in this feasibility trial, which will inform the cost evaluation in the subsequent study on efficiency.

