### Chemotherapy for LAPC

Systemic chemotherapy is the standard treatment for unresectable PC.^4^ Despite advances in drug therapy for pancreas cancer over the last 20 years, the overall survival (OS) and progression-free survival (PFS) of these patients have not significantly improved.^5^ Furthermore, a meta-analysis reported that chemoradiation is not superior to chemotherapy alone in patients with LAPC, with comparable OS and higher rates of grade 3–4 adverse events (AEs).^6^

In the UK National Institure of Clinical Excellence (NICE) guidelines, published in 2018, recommend systemic combination chemotherapy for both locally unresectable and metastatic PC.^7^ NICE recommends first-line combination chemotherapy with 5-FluoroUracil, Leucovorin, Irinotecan and Oxaliplatin (FOLFIRINOX) in fit patients (Eastern Cooperative Oncology Group performance status of 0–1). In patients with comorbidities and restricted activities, or those unable to tolerate this regime, NICE recommends gemcitabine alone or gemcitabine-based therapy.^6^ Although FOLFIRINOX shows the best objective response in PC,^8 9^ it is associated with more frequent and severe side effects, including neutropenia, diarrhoea and peripheral neuropathy.^10^

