### Assessment of feasibility

One aspect of the feasibility evaluation of this trial is to evaluate the ability to recruit patients with LAPC into a trial of this nature. The average number of patients with unresectable LAPC within UK specialist pancreas units is 60 patients per centre per year (Royal Free Hospital London audit data 2017, unpublished). Staging following FOLFIRINOX chemotherapy will demonstrate localised but unresectable disease in approximately 40 out of 60 patients (65%).^12^ These patients will be eligible for the LAP-PIE trial. We anticipate recruiting 20% of potential participants to the LAP-PIE trial, which equates to eight per centre per year. Recruitment within five centres would allow 40 UK patients per year. A recruitment time of 15 months would allow 50 patients to be recruited.

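### The two forecasts behind 50 patients in 15 months use incompatible inputs; the planned 20% uptake on the stated site-opening schedule gives about 42, and criterion A has no deadline

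*Protocol article*

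**What the plan says.** The abstract sets the target: "Fifty patients from up to seven specialist pancreas centres in the UK will be recruited over a period of 15 months".

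Two sections of the protocol article then justify it.

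- *Study design and setting* gives an enrolment period of 15 months and rests it on this forecast: "assuming a recruitment rate of 0.8 patients per site per month across seven UK centres and an opening site rate of 0.5 per month".
- *Assessment of feasibility* builds up from the patient pool. It starts from 60 patients with unresectable disease per centre per year and takes about 40 of them to be still localised and unresectable after FOLFIRINOX. Of these it says: "These patients will be eligible for the LAP-PIE trial". It continues: "We anticipate recruiting 20% of potential participants to the LAP-PIE trial, which equates to eight per centre per year". It concludes: "Recruitment within five centres would allow 40 UK patients per year. A recruitment time of 15 months would allow 50 patients to be recruited".

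Under *Outcomes*, recruitment rate is listed as part of the primary outcome. Under *Progress to full trial*, criterion A is recruitment of 50 patients over the study sites, with no period given, and criterion B is a consent rate of 20±11%.

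**The concern.** Both sections arrive at 50 patients in 15 months, so they look like mutual support. They differ on all three inputs that determine accrual: the rate per site, the number of sites, and whether sites open gradually or are all open from the start. The text does not reconcile them.

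This matters because recruitment is the main question of this feasibility trial, and the full trial will be planned from the answer. An observed rate of 0.7 per open site-month would be better than one section expects and worse than the other expects. A trial that achieves exactly the 20% uptake it plans for should expect to be short of 50 at month 15 on its own opening schedule. Criterion A does not say how that result is to be read.

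**Working it through.** **Method.** Expected recruits = open site-months × recruits per site per month.

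**Inputs.** From *Study design and setting*: 0.8 per site-month, seven sites, 0.5 sites opened per month (one every two months), 15 months. From *Assessment of feasibility*: 40 eligible per centre per year, 20% recruited, five centres, 15 months, no staggering mentioned.

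**Step 1: reproduce the forecast in *Study design and setting*.** Sites open at months 0, 2, 4, 6, 8, 10 and 12. Site-months by month 15: 15 + 13 + 11 + 9 + 7 + 5 + 3 = 63. Recruits: 63 × 0.8 = 50.4. The stated 50 is reproduced.

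Of the opening conventions tried, only a first site at month 0 gives 50. A first site at month 1, or a continuous ramp, gives 56 site-months and 56 × 0.8 = 44.8. A first site at month 2 gives 49 site-months and 49 × 0.8 = 39.2. With all seven sites open throughout, the total would be 7 × 15 × 0.8 = 84. The month-0 convention is therefore used below; it is also the most favourable of the staggered ones.

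**Step 2: reproduce the forecast in *Assessment of feasibility*.** 20% × 40 = 8 per centre per year; 8/12 = 0.667 per site-month. Site-months: 5 × 15 = 75. Recruits: 75 × 8/12 = 50.0. The stated 50 is reproduced, but only with all five centres open for all 15 months.

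**Step 3: compare the inputs.**

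| | Study design and setting | Assessment of feasibility |
|---|---|---|
| Rate per site-month | 0.8 | 0.667 |
| Rate per site-year | 9.6 | 8 |
| Share of 40 eligible | 9.6/40 = 24% | 8/40 = 20% |
| Sites | 7 | 5 |
| Opening | one every two months | all from month 0 |
| Site-months by month 15 | 63 | 75 |
| Expected recruits | 50.4 | 50.0 |

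Rounding does not close the gap: 0.667 rounds to 0.7, and 63 × 0.7 = 44.1.

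**Step 4: apply the planned 20% uptake to the stated opening schedule.** 63 × 8/12 = 42.0 expected at month 15. Seven sites are open from month 12, so accrual after month 15 is 7 × 8/12 = 4.67 per month. The remaining 8 patients take 8/4.67 = 1.7 months, which puts the fiftieth at about 16.7 months. The article prints 65% beside 40 out of 60; taking 65% literally gives 39 eligible, 7.8 per centre per year, and 63 × 7.8/12 = 41.0.

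**Step 5: uptake needed for 50 by month 15 on that schedule.** 50/63 = 0.794 per site-month; 0.794 × 12/40 = 23.8%.

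**Step 6: chance variation.** If accrual is Poisson (an assumption), the probability of at least 50 by month 15 is about 0.125 with mean 42.0 and about 0.54 with mean 50.4.

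**Secondary check: the pool of 40.** *Chemotherapy for LAPC* says that FOLFIRINOX is recommended "in fit patients (Eastern Cooperative Oncology Group performance status" of 0–1), with gemcitabine-based treatment for others. *Participants* lists exclusions such as kidney disease, coagulopathy, neurological conditions and contraindications to general anaesthesia. The 40 carry no deduction for either. If a fraction f of the 40 is truly eligible, eight recruits per centre per year needs an uptake of 20%/f. The article gives no value for f. Purely as an assumed range, f = 0.75 requires 27% and f = 0.5 requires 40%.

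**The case against.** Five points can be made for the plan.

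- **Each forecast is arithmetically sound on its own inputs.** This stands. The fault is that both are offered for the same trial.
- **The 42 combines a rate from one section with an opening schedule from the other, and the pool calculation may be only a rough check beside an operational forecast.** It is true that neither section prints this combination. But 20% is the article's only stated uptake and the staggered schedule is its only stated opening plan, so a reader is entitled to put them together. A rough check that needs every centre open on day 0 does not support a plan in which sites open one every two months.
- **An uptake of 24% lies within criterion B's 20±11%, that is 9% to 31%.** This stands: 0.8 per site-month does not conflict with B. Nor does the article say that B's consent rate has the same denominator as the 20% of potential participants.
- **The rates 0.667 and 0.8 are planning assumptions, not thresholds.** This also stands. *Outcomes* sets no threshold for recruitment rate, and *Progress to full trial* uses neither figure.
- **Criterion A has no deadline.** A reader might infer that a trial performing exactly at 20% fails criterion A. The document does not support that. As printed, such a trial would be expected to meet A at about 16.7 months. The failure appears only if the 15 months stated elsewhere is read into A, and even then 42 is an expectation, so a shortfall is likely rather than certain.

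**Conclusion.** The contradiction is real. The same 50 patients in 15 months rests on 0.8 per site-month in seven sites opening gradually (24% of 40) in one place and on 0.667 per site-month in five centres always open (20% of 40) in another. At the planned 20% on the stated schedule, the expectation is about 42 at month 15, a shortfall of about 8, or a slip of about 1.7 months to reach 50. This assumes a first site at month 0, constant rates and 40 eligible patients per centre per year.

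It does not follow that such a trial fails to progress: criterion A is untimed, so it gives no answer either way. That silence is the second half of the point.

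The undiscounted pool of 40 makes the feasibility forecast optimistic, but by an amount that the article does not allow one to calculate. It is secondary, and the contradiction does not depend on it.

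This should be fixed, because it concerns the trial's primary outcome and a progression criterion. It does not affect any treatment comparison or the sample size of 50.

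**What to change.** 1. Use one recruitment model in *Study design and setting* and *Assessment of feasibility*, with the same rate, number of sites and opening schedule. Either keep 20% (0.667 per site-month) with staggered opening and restate the expectation as about 42 patients in 15 months, or about 17 months for 50; or keep 0.8 per site-month and restate the uptake as 24% of 40, that is 9.6 per centre per year.
2. Write criterion A as 50 patients within the stated recruitment period, whichever period the chosen model supports.
3. In *Assessment of feasibility*, either reduce the 40 for patients not fit for FOLFIRINOX and for the listed exclusions, giving the source of the reduction, or say that no deduction has been made and that the 40 is an upper figure.

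The cost is rewording and about a page of recalculation. If 20% is kept, the stated forecast becomes less favourable. No extra patients are needed.

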**Figure 1 F1:**
[figure not shown]
Trial flow diagram. CTCAP, CT chest abdomen pelvis; FOLFIRINOX, 5-FluoroUracil, Leucovorin, Irinotecan and Oxaliplatin; IRE, irreversible electroporation; LAPC, Locally Advanced Pancreatic Cancer; OS, overall survival; PFS; progression free survival; QoL, quality of life; SoC, standard of care; sMDT, specialist multidisciplinary team.

**Table 1 T1:** Schedule of enrolment, interventions and assessments of the LAP-PIE trial

Timepoint	Study period									
	Enrolment	Allocation	Post-allocation follow-up time points							Close-out
	-*t_1_*	0	*Pre-IRE*	*6 hours post-IRE*	*6 days post-IRE*	*3 months*	*6 months*	*9 months*	*12 months*	
Enrolment:										
Eligibility screen	X									
PIS given	X									
*Systemic treatment with FOLFIRINOX*	X									
*sMDT*	X									
*Informed consent*	X									
Allocation		X								
Interventions:										
*IRE (intervention)*										
*Systemic chemotherapy (SoC)*										
Assessments:										
*CT CAP*	X					X	X	X	X	
*Blood tests*	X		X	X	X	X	X	X	X	X
*HRQoL*						X	X	X	X	X
*Complications*						X	X	X	X	X

CT CAP, CT chest abdomen pelvis; FOLFIRINOX, 5-FluoroUracil, Leucovorin, Irinotecan and Oxaliplatin; HRQoL, health-related quality of life; IRE, irreversible electroporation; LAP-PIE, locally advanced pancreatic cancer with percutaneous irreversible electroporation; PIS, patient information sheet; sMDT, specialist multidisciplinary team; SoC, standard of care.

### Participants

Adults (≥18 years) with LAPC following first-line chemotherapy with FOLFIRINOX will be eligible. Only patients who have completed FOLFIRINOX as their first-line chemotherapy will be eligible. Patients who have received FOLFIRINOX as second-line therapy prior to inclusion will not be eligible. Following FOLFIRINOX chemotherapy, patients will be restaged with CT chest, abdomen and pelvis (CAP)±an *fluorodeoxyglucose* (FDG) positron emission tomography (PET) scan, depending on local site protocols. The imaging will be reviewed in a specialist multidisciplinary team (sMDT) meeting.

Patients with borderline resectable disease will be excluded. The definition for this is summarised in table 2. Other exclusion criteria include untreated biliary or gastric outlet obstruction, coagulopathy, chronic kidney disease (CKD) stage ≥3 (the criteria for CKD stage 3 is an estimated glomerular filtration rate of between 30 and 59),^26^ indwelling electrical devices, abdominal varices precluding safe access to the pancreas and significant comorbidities that would contraindicate general anaesthesia and neuromuscular blockade. A contraindication, as per manufacturer guidance, is epilepsy as the electrical discharges from IRE treatment may in theory result in seizure activity through pulsatile brain stimulation. Although the overall impact of IRE on seizure activity and neurological conditions remains unclear,^27^ in the interest of robust patient safety, patients with neurological conditions will be excluded. The full inclusion and exclusion criteria are summarised in figure 2.

**Figure 2 F2:**
[figure not shown]
Inclusion and exclusion criteria of the LAP-PIE trial. CKD, chronic kidney disease; FOLFIRINOX, 5-FluoroUracil Leucovorin, Irinotecan and Oxaliplatin; Hb, haemoglobin; IR; interventional radiologist; IRE, irreversible electroporation; LAP-PIE, locally advanced pancreatic cancer with percutaneous irreversible electroporation; sMDT, specialist multidisciplinary team.

**Table 2 T2:** Definition of borderline resectable pancreatic cancer^18^

	Borderline resectable	Unresectable
Coeliac artery	Tumour without encasement or abutment	Tumour contact >180°
Superior mesenteric artery	Tumour abutment ≤180°	Tumour contact >180°
Superior mesenteric vein (SMV)/portal vein (PV)	Tumour abutment of SMV/PV>180° or abutting ≤180° with irregularity of the vein ±thrombosis with anatomical structures that still permit safe and complete resection with vein reconstruction	SMV/PV unreconstructible secondary to tumour involvement or occlusion
Common hepatic artery	Reconstructible short segment abutment	Unreconstructible interface between tumour mass and vessel

Adapted from Callery *et al*.^18^

### Randomisation

Following confirmation of eligibility randomisation will be performed by the Liverpool Clinical Trials Centre (LCTC) using a web-based randomisation procedure. The LCTC will inform local centres of the treatment arm and the local LAP-PIE Clinical Trials Nurse will inform the patient and make arrangements for clinical review and the date for the chosen therapy.

### Intervention

#### Pancreas IRE

Patients will be invited for an anaesthetic preassessment to ensure that they are fit enough to undergo IRE under general anaesthesia prior to being booked for hospital admission. Patients will be admitted to a ward or radiology admissions unit under joint clinical care of a pancreas interventional radiologist and one of the other site leads (surgery, Oncology).

The CT CAP performed on completion of FOLFIRINOX will be used by the interventional radiologist to plan IRE therapy. Under general anaesthesia, IRE will be delivered percutaneously using CT guidance. Timing of the procedure will be coordinated with the treating oncologist to ensure bone marrow recovery following FOLFIRINOX chemotherapy. A broad-spectrum antibiotic, based on individual centres’ first-line prophylaxis for Gastro-Intestinal (GI) infection, will be given prior to the procedure and 6 hours and 12 hours following IRE.

The IRE procedure will be standardised to use between 2 and 6 IRE needles depending on the size, shape and relationship of critical structures to the tumour, with a maximum interelectrode distance of 2 cm. A treatment margin of at least 0.5 cm will be maintained. The needle placement prior to treatment will be recorded on CT.

IRE therapy will be delivered using ECG synchronisation to ensure that the pulse is delivered during diastole. The length of the electrical pulse and amperage will be decided by the treating interventional radiologist and will be between 70 μs and 100 μs with an amperage of between 20 AMPs and40 AMPs. The treating interventional radiologist will have relevant expertise in IRE procedures with a minimum of five IRE procedures on liver or pancreas performed previously.

Following IRE therapy, full blood count, liver function tests, coagulation, renal function and amylase (or lipase) will be monitored and patients will be admitted for a minimum of 24 hours to ensure adequate pain management and to monitor and manage any immediate complications. Participants will be discharged with pain relief as required and Deep Vein Thrombosis (DVT) prophylaxis for 4 weeks.

The intraoperative imaging will be reviewed by the lead radiologist at each site and if the entire tumour has been treated based on these images, the procedure will be deemed as successful. The technical success will be confirmed by central review. Contrast CT follow-up scans will be assessed for evidence of tumour growth as indicated by mass enlargement or increased vascularity. In the absence of tumour growth, the procedure will be considered successful at follow-up. At the end of the follow-up period, serial imaging will be analysed, and the tumour staged. Local disease control will be evaluated according to the Response Evaluation Criteria in Solid Tumours. This will be performed by the radiology leads at each site and confirmed by a central review.

Following IRE, patients in this arm will be offered second-line chemotherapy, which is the current standard of care. The drug choice and timing of chemotherapy will be decided by treating oncologists and will adhere to NICE guidelines.

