### Outcomes

The primary objective of the LAP-PIE trial is to ascertain feasibility of such a trial concept. In particular, the ability to identify and recruit LAPC patients at the selected sites to the LAP-PIE trial will be evaluated. The primary outcome consists of recruitment rate, number of screening failures, number of patients completing study pathway as per protocol and trial withdrawal rate.

The secondary objectives of the LAP-PIE trial aim to assess the practicality and technical success rate of pancreas IRE treatment. Technical success will be determined by the interventional radiologist performing the procedure. The procedure will be deemed to be technically successful if the entire tumour has been treated based on imaging performed during the intervention. Completion and complication rates of IRE procedures will be evaluated. The proportion of patients in whom percutaneous IRE was successful, defined as no local growth on follow-up, will be determined as will the proportion of patients who became eligible for surgery following IRE and the R0/R1 resection rates in these participants. Acceptability of pancreas IRE therapy to patients and their clinicians, rate of withdrawal from the study and outcome measures including OS (measured from randomisation), PFS and QoL will be evaluated. Finally, health-related costs, including indicative costs related to health resource use in both arms, social costs of attending IRE treatment such as cost of travel to and from a tertiary centre, time off work and social support costs will be evaluated.

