### Progress to full trial

The criteria to progress to a subsequent full trial will be determined quantitatively as (A) the ability to recruit 50 patients to the study across the study sites (B) a consent rate of 20±11%, (C) overall technical success rate of 50±14% and (D) a loss to follow-up of 10±8%.

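### Technical success and local control are read first by the operator or the unmasked site lead, central review is described only as confirming them, and no rule says which reading counts

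*Protocol article*

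**What the plan says.** Study design and setting: "It is an open-label study". The article describes no masked image reader.

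On technical success, two sections name different judges:
- Outcomes: "Technical success will be determined by the interventional radiologist performing the procedure".
- Pancreas IRE: "The intraoperative imaging will be reviewed by the lead radiologist at each site", and the procedure counts as successful if those images show the whole tumour treated. Then: "The technical success will be confirmed by central review".

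On local control, Pancreas IRE says: "At the end of the follow-up period, serial imaging will be analysed, and the tumour staged". The criterion follows: "Local disease control will be evaluated according to the Response Evaluation Criteria in Solid Tumours". The readers are then named: "This will be performed by the radiology leads at each site and confirmed by a central review". Outcomes lists the proportion of IRE patients without local growth at follow-up as a secondary measure.

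Progress to full trial makes technical success one of four criteria: "overall technical success rate of 50±14" per cent. Local control is not among the four.

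**The concern.** The site lead who reads local control also reviews the images taken during IRE, and so knows which patients were treated. For technical success, the wording under Outcomes lets the operator grade his or her own procedure. Both readers have a natural interest in a good result.

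A central review corrects this only if it is a separate reading. If the reviewer starts from the site's answer and is asked to agree or disagree, borderline cases will tend to stay where the site put them. The text describes the review only as confirmation and gives no rule for disagreement, so the safeguard may be weaker than it looks.

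Two uses of the data are exposed. Technical success helps decide whether a full trial goes ahead. Local control is a reported measure of how well IRE worked, in a trial meant to supply preliminary efficacy data for the design of the next one.

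**Working it through.** This is mainly a question of text, so the passages are compared first and the arithmetic only gives the scale.

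**Who decides what**

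| Outcome | Outcomes section | Pancreas IRE section | Role of central review | Rule on disagreement |
|---|---|---|---|---|
| Technical success | Operating radiologist | Site lead radiologist | Confirms | None given |
| Local control | No reader named | Site radiology leads | Confirms | None given |
| PFS | No reader named | Not mentioned | Not stated | None given |

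The operator and the site lead may or may not be the same person; the article does not say. Either way, the two sections assign technical success differently, and only one of them mentions central review.

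**Scale**

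Inputs: 50 patients randomised equally (Sample size calculation), so 50/2 = 25 in the IRE arm if all are treated and read.

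- One reclassified reading: 1/25 = 4 percentage points.
- The plan's ±14 is reproduced as a 95% half-width at n = 50: 1.96 × √(0.5 × 0.5/50) = 13.9 points.
- Technical success can be observed only in IRE patients. At n = 25 the half-width is 1.96 × √(0.5 × 0.5/25) = 19.6 points. Four reclassified readings (4/25 = 16 points) exceed 14 but lie within 19.6.
- Suppose criterion C is a floor at 50 − 14 = 36% (an assumption; the article does not say how the range is applied). Then 9/25 = 36% meets it and 8/25 = 32% does not. A single reading decides the matter only if the result falls at that boundary.

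**Illustration for local control, all rates assumed**

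Let p be the true proportion controlled, m the share of growth cases misread locally as controlled, and q the share of those that central review overturns. The upward shift in the IRE arm is (1 − p) × m × (1 − q). With p from 40% to 60% and m from 10% to 30%:

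- q = 0: from 0.4 × 0.1 = 4 points to 0.6 × 0.3 = 18 points.
- q = 0.5: from 2 to 9 points.
- q = 1: 0 points.

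The documents give none of p, m or q. The range shows only that the result depends on how freely the central review departs from the local reading, which is the feature left open.

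**The case against.** The strongest reply is that the article never says the central reviewer sees the site result. Confirmation could mean an independent second reading. Reader masking, reading order and adjudication often sit in a full protocol or imaging charter, and neither is shown here. This stands in part: a reader might infer that the central review is in fact anchored, and the text does not establish that. It establishes that a local reading comes first, that the central step is described only as confirming it, and that two sections name different judges for technical success. An unseen charter might clarify the first two, but the conflict between the two sections is in the article itself.

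A reader might also infer that PFS is biased in favour of IRE. The article names no PFS reader, and the local-control sentence sits in the IRE section. A between-arm bias follows only if the same readings feed PFS.

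A third tempting reading is that a few generous calls would overturn the progression decision, for example by moving 50% to 66%. That example assumes four misreadings, none of them overturned. It sets a 25-patient shift against a margin that matches 50 patients, and it starts from a value that already meets criterion C. It does not show a changed decision.

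Finally, ablation changes on CT may reveal the arm, so masking can be incomplete. That is true of follow-up scans. For technical success, allocation masking is irrelevant because only IRE patients are assessed. Independence from the site result is achievable in both cases.

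**Conclusion.** The point holds as a weakness in how two secondary readings are fixed. As worded, technical success is settled by the operator or the site lead, and local control by an unmasked site lead. Central review can be anchored to those readings, and no reading is named as the one to analyse.

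Each reclassified patient is worth 4 points, assuming about 25 IRE patients are read. The direction would plausibly favour IRE, but the size is unknown because no misreading rate is given. Effects on PFS are conditional on the same readings being used. The primary outcome (recruitment, screening failures, pathway completion and withdrawal) is untouched, and the trial is not powered for effectiveness. This is a worthwhile improvement and does not threaten the trial's main purpose.

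**What to change.** 1. Reconcile Outcomes with Pancreas IRE so that one statement says who determines technical success.
2. State that the central reviewer reads the procedural and follow-up CTs without seeing the site result and, for follow-up CTs, without allocation where the images allow.
3. Name the central reading as the analysis value for technical success (criterion C) and local control. Apply the same rule to PFS if these readings feed it.
4. Report how often site and central readings disagree, and in which direction. For a feasibility trial this is useful information for planning the next one.

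The cost is a wording change and some extra time for the central reviewer who is already planned. No extra reader is needed, and the sample size does not change.
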